#### Recruitment strategy

2.3.1

The study will be conducted from January 2025 to January 2026 at the First Affiliated Hospital of Guangzhou University of Chinese Medicine. Participants will be recruited via hospital advertisements and online platforms.

#### Written informed consent

2.3.2

Eligible participants will receive detailed written information about randomization (verum/sham/wait-list), potential benefits/risks, and voluntary withdrawal rights. Consent forms (Supplementary material 2) will be signed prior to enrollment.

### Randomization, allocation, concealment and blinding

2.4

Randomization will be generated with the use of a random-number method via a computerized central randomization system. Eligible PD patients will be allocated in a 1:1:1 ratio to three groups: verum acupuncture, sham acupuncture, or waitlist control. After confirming eligibility, investigators will request group assignment via the centralized system, which automatically assigns and communicates the allocation to the investigator for intervention implementation. The randomization sequence will remain concealed on a secure server until completion of participant enrollment, data collection, and analysis to prevent selection bias.

To ensure methodological rigor, blinding will be implemented between the verum and sham acupuncture groups via a sham placebo acupuncture device (SPAD; Patent No. 2023215153288). The participants in both groups will receive treatments in private rooms to prevent cross-group communication. Outcome assessors, independent third-party personnel blinded to group allocations, will conduct all the clinical evaluations. A primary blinding code will be applied to the statistical database, ensuring that statisticians remain unaware of group assignments during analysis.

Owing to the inherent nature of acupuncture interventions, full blinding between acupuncture groups (verum/sham) and the wait-list control group is unattainable. However, stringent separation of study phases (recruitment, intervention, assessment) and adherence to predefined standard operating procedures (SOPs) minimize bias risks. In cases of serious adverse events (SAEs) requiring urgent unblinding (e.g., life-threatening complications), the principal investigator will access the allocation code via a sealed envelope stored in a secure location, document the reason, and report to the ethics committee within 24 h. Post-trial, the success of participant blinding will be evaluated via structured questionnaires. If blinding is compromised, we will perform sensitivity analyses by including blinding success as a covariate in the primary outcome models to assess its impact on treatment effect estimates.

### Intervention

2.5

All PD participants will receive eight sessions (twice weekly for 4 weeks) of either verum or sham acupuncture. The regimen was derived from our clinical practice and informed by a pilot study that demonstrated significant clinical improvements, with due consideration of the need to balance treatment intensity and participant burden. The wait-list control group will receive no acupuncture during the observation period but will be offered the intervention post-trial. Patients on antiparkinsonian medications (e.g., levodopa) will maintain their regimen, with levodopa equivalent doses (LED) calculated at baseline. During the trial, medication adjustments are strongly discouraged; however, if any adjustment becomes clinically necessary, the change will be fully documented in case report forms (CRFs). HCs will undergo baseline MRI only, without interventions.

The verum and sham acupuncture groups will utilize the SPAD to ensure participant blinding. After standard skin disinfection, the SPAD is affixed to the target acupoint. For verum acupuncture, a sharp needle is inserted through the SPAD base to penetrate the skin. For sham acupuncture, a blunt-tip needle retracts upon contact with the skin, whereas microneedles within the SPAD simulate tactile penetration, replicating the deqi sensation without actual insertion. Figure 2 illustrates the blinding setup.

**Figure 2 F2:**
[figure not shown]
Qihuang needle and blind operation. **(A)** Qihuang needle, comprises four components: tip, body, handle, and protective cap. **(B)** A sham placebo acupuncture device (SPAD) integrates verum and sham needles. During application, the SPAD is attached to acupoints. For verum acupuncture, sharp needles penetrate the skin through the SPAD base. In contrast, sham needles feature a retractable blunt tip; upon contact with the base, internal microneedles within the SPAD simulate tactile penetration without skin puncture.

#### Verum acupuncture group

2.5.1

The QNT employs disposable sterile acupuncture needles (Approval: 20202200072; 0.5 × 50 mm; Figure 2A) with a unique design: a hollow body, transparent handle, and arc-shaped tip. This configuration enhances mechanical strength and maneuverability, facilitating precise needle manipulation, robust deqi (sensation of soreness, numbness, or distension), reduced pain, and minimal vascular injury. A protective cap is used during acupoint transitions to prevent accidental needle-tip exposure.

On the basis of meridian-muscle theory and clinical expertise, participants in the verum acupuncture group will receive two weekly sessions over 4 weeks (8 sessions total) with the following protocol: acupoint prescription 1 (bilateral): EX-HN3 (Yintang), LI10 (Shousanli), TE4 (Yangchi), BL24 (Qihaishu), GB33 (Xiyangguan), and BL58 (Feiyang). Acupoint prescription 2 (bilateral): GV20 (Baihui), TE9 (Sidu), PC7 (Daling), BL20 (Pishu), BL40 (Weizhong), and GB34 (Yanglingquan). This sequence will be repeated weekly for 4 weeks. Acupoint localization follows the WHO Standard Acupuncture Point Locations in the Western Pacific Region (19) (Table 2, Figure 3).

**Table 2 T2:** Location of acupoints.

Acupoint	Location
Acupoint prescription 1	
EX-HN3 (Yintang)	On the head, between the right medial end of the eyebrow and the left one.
LI10 (Shousanli)	On the posterolateral aspect of the forearm, on the line connecting LI5 with LI11, 2 Bcun inferior to the cubital crease.
TE4 (Yangchi)	On the posterior aspect of the wrist, in the depression ulnar to the extensor digitorum tendon, on the dorsal wrist crease.
BL24 (Qihaishu)	In the lumbar region, at the same level as the inferior border of the spinous process of the third lumbar vertebra (L3), 1.5 B-cun lateral to the posterior median line.
GB33 (Xiyangguan)	On the lateral aspect of the knee, in the depression between the biceps femoris tendon and the iliotibial band, posterior and proximal to the lateral epicondyle of the femur.
15.6-7.4,-38.3241ptBL58 (Feiyang)	On the posterolateral aspect of the leg, between the inferior border of the lateral head of the gastrocnemius muscle and the calcaneal tendon, at the same level as 7 Bcun proximal to BL60.
Acupoint prescription 2	
GV20 (Baihui)	On the head, 5 B-cun superior to the anterior hairline, on the anterior median line.
TE9 (Sidu)	On the posterior aspect of the forearm, midpoint of the interosseous space between the radius and the ulna, 5 B-cun distal to the prominence of the olecranon.
PC7 (Daling)	On the anterior aspect of the wrist, between the tendons of palmaris longus and the flexor carpi radialis, on the palmar wrist crease.
BL20 (Pishu)	In the upper back region, at the same level as the inferior border of the spinous process of the 11th thoracic vertebra (T11), 1.5 B-cun lateral to the posterior median line.
BL40 (Weizhong)	On the posterior aspect of the knee, at the midpoint of the popliteal crease.
GB34 (Yanglingquan)	On the fibular aspect of the leg, in the depression anterior and distal to the head of the fibula.

**Figure 3 F3:**
[figure not shown]
Location of acupoints.

After standard skin disinfection, needles are swiftly inserted subcutaneously via the SPAD. Body and limb acupoints are inserted perpendicularly to a depth of 10–15 mm, whereas cranial acupoints undergo subcutaneous insertion at a depth of 5–10 mm. Upon achieving deqi, the needle is withdrawn to the entry point, followed by a Hegu manipulation (30–45 ° oblique redirection in opposing planes; Figure 2B) before removal.

#### Sham acupuncture group

2.5.2

The participants will undergo procedures identical to those of the verum group, including acupoint selection and SPAD application, but non-penetrating blunt-tip needles will be used. The sham needles mimicked tactile stimulation without skin penetration, ensuring equivalent sensory feedback. Posttrial, the sham group participants will receive eight complimentary verum acupuncture sessions.

#### Wait-list control group

2.5.3

During the 8-week observation period, wait-list controls will receive no acupuncture. To meet ethical standards, they will be offered eight free verum acupuncture sessions post-study, identical to the verum group's protocol.

### Outcome measures

2.6

#### Clinical outcomes

2.6.1

This trial is primarily designed to detect neuroplastic changes via multimodal MRI. Accordingly, the primary endpoint is the change in multimodal MRI biomarkers, whereas all clinical outcomes and biomechanical indices are designated as exploratory endpoints.

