This study aims to: (1) conduct a triple-arm randomized controlled trial to evaluate the clinical efficacy of QNT in PD, and (2) integrate multimodal MRI to map functional connectivity reorganization, gray matter volume changes, white matter integrity, nigral iron deposition, and neuromelanin preservation, thereby identifying neuroplasticity targets induced by acupuncture.

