#### Neuroimaging data analysis

2.9.2

Neuroimaging data will be analyzed according to standardized pipelines, with comprehensive details provided in Supplementary material 3. For VBM, the CAT12 toolbox (SPM12, version r1720; CAT12, r1720) will be used for bias correction, tissue segmentation, and spatial normalization to MNI space. Whole-brain VBM results will be reported at cluster-level family-wise error (FWE) corrected *p* < 0.05 with an initial voxel-level threshold of *p* < 0.001. Resting-state fMRI data will be preprocessed using DPABI v6.1. Preprocessing will include discarding the first 10 volumes, slice timing correction, realignment, normalization to MNI space, spatial smoothing (6-mm FWHM), nuisance regression (Friston-24 motion parameters and WM/CSF signals), detrending, and bandpass filtering (0.01–0.08 Hz). Volumes with framewise displacement (FD) > 0.5 mm will be censored using scrubbing regressors; participants with >20% censored volumes or with maximum head motion >3.0 mm translation or 3.0° rotation will be excluded. Seed-based functional connectivity will be computed using predefined seeds from the Automated Anatomical Labeling (AAL) atlas (bilateral putamen, caudate, globus pallidus, and thalamus; seed coordinates are provided in Supplementary material 3). Voxel-wise connectivity maps (Fisher's z-transformed) will be assessed using cluster-level FWE correction (voxel *p* < 0.001; cluster *p* < 0.05). To address multiple comparisons arising from testing multiple seeds, seed-level multiplicity will be controlled using false discovery rate (FDR; Benjamini–Hochberg) across seeds (*q* < 0.05). In addition, the bilateral putamen will be designated *a priori* as the primary seed of interest, whereas results from the remaining seeds will be considered secondary/exploratory and interpreted with FDR control across seeds. DTI data will be processed using DTIStudio v3.0.3 (and the NODDI toolbox in MATLAB R2013b, if applicable). Fractional anisotropy (FA), mean diffusivity (MD), radial diffusivity (RD), and axial diffusivity (AD) will be computed. Regions of interest (substantia nigra, putamen, caudate) will be manually delineated on FA color maps by two independent raters blinded to group and time point, with inter-rater reliability assessed using intraclass correlation coefficients (ICC; ICC > 0.80 required). ROI-based statistical comparisons will apply Bonferroni correction within each predefined ROI family. SWI phase images will undergo high-pass filtering (32 × 32) before manual delineation of substantia nigra (SN) area and measurement of SN pars compacta (SNc) width. NM-MRI SNc width will be measured in the dorsoventral direction on the optimal axial slice using the ADW4.6 workstation. ICC will be assessed for all manual measurements, and the average of the two raters will be used for analysis. All statistical tests will be two-tailed with significance set at *p* < 0.05 after correction.

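### The primary endpoint is an unranked set of MRI biomarkers across five modalities, with error control stated only within each modality and no between-arm contrast named for the primary claim

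*Protocol article*

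**What the plan says.** Section 2.6.1 (Clinical outcomes) states that "the primary endpoint is the change in multimodal MRI biomarkers" and classes every clinical and biomechanical measure as exploratory. The Introduction sets the imaging aim as to "map functional connectivity reorganization, gray matter volume changes, white matter integrity, nigral iron deposition, and neuromelanin preservation", which makes five modalities. Section 2.3 refers to the primary neuroimaging endpoints in the plural and claims that 69 patients give enough power for them.

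Section 2.9.2 (Neuroimaging data analysis) gives the error control modality by modality:

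- VBM: "Whole-brain VBM results will be reported at cluster-level family-wise error (FWE) corrected *p* < 0.05".
- Resting-state fMRI: cluster-level FWE for each connectivity map, and "seed-level multiplicity will be controlled using false discovery rate (FDR; Benjamini–Hochberg) across seeds". The bilateral putamen is set apart in advance "as the primary seed of interest, whereas results from the remaining seeds will be considered secondary/exploratory", with FDR control across seeds mentioned again for the latter.
- ROI measures: "ROI-based statistical comparisons will apply Bonferroni correction within each predefined ROI family". What makes up a family is not defined in the article.
- Overall: "All statistical tests will be two-tailed with significance set at *p* < 0.05 after correction".

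The trial has three arms, so each biomarker allows up to three pairwise contrasts. Section 2.9.2 does not say which of them carries the primary claim.

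**The concern.** A primary endpoint should tell the reader which result decides the question. Here it is a collection, and each stated correction ends at the border of its own modality. Read as written, the text lets gray matter, connectivity, diffusion, iron or neuromelanin each be reported as meeting the primary endpoint on passing its own 0.05 threshold. The only ranking, the putamen seed, sits inside resting-state fMRI and does not make that modality primary.

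At stake is the headline question of whether QNT changes the brain. If any of five routes can answer yes, a chance finding in one of them is far more likely than 5%, and a reader of the report cannot tell a planned primary result from the best of several.

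The seed rule adds a smaller uncertainty, because the threshold for the putamen depends on whether it belongs to the FDR family.

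**Working it through.** **The plan's own figures.** The article states no overall type I error for the primary endpoint, so there is none to reproduce. Its imaging sample size does reproduce: 20 per group with 10% attrition gives 20 / 0.90 = 22.2, rounded up to 23, and 3 × 23 = 69.

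**Inputs.** Two-sided 0.05 after within-family correction (section 2.9.2); five modalities (Introduction); four DTI metrics, two SWI measures and one NM-MRI width (section 2.9.2). Assumptions: each family is held at 0.05 by its own correction, one contrast is tested per family, and one positive family is enough for the claim.

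**Independent tests.** The family-wise error for k families is 1 − (1 − 0.05)^k.

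- k = 5, one per modality: 1 − 0.95^5 = 22.6%.
- k = 9, counting VBM 1, putamen connectivity 1, DTI metrics 4, SWI measures 2, NM-MRI 1: 1 − 0.95^9 = 37.0%.

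**Correlated tests.** The documents give no correlation between biomarkers, so a range was simulated with equally correlated two-sided z-tests at 1.96:

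| Correlation | 5 tests | 9 tests |
|---|---|---|
| 0 | 23% | 37% |
| 0.3 | 21% | 33% |
| 0.5 | 18% | 27% |
| 0.7 | 15% | 20% |
| 0.9 | 10% | 12% |

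With nine tests in which the DTI metrics are correlated 0.6 with each other and the two SWI measures likewise, the result is 33% if modalities are independent and 31% if they are correlated 0.3. Complete dependence would give 5%. The Bonferroni ceilings, which hold under any dependence, are 5 × 0.05 = 25% and 9 × 0.05 = 45%.

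**Seed rule.** There are four bilateral seeds. If the putamen is tested on its own, its threshold is 0.05. If it is inside a Benjamini–Hochberg family of four and is the only seed with a signal, it must reach 0.05 / 4 = 0.0125. If left and right count separately, it must reach 0.05 / 8 = 0.00625. The text allows each of these.

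**After the fix.** Five modalities at 0.05 / 5 = 0.01 each: 1 − 0.99^5 = 4.9% under independence. A single primary test: 5%.

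**The case against.** The best defence is that section 2.3 calls the trial exploratory and mechanistic, and that no sentence says one positive modality means success. The set could even be read as requiring all five, which would not inflate the error. It is true that the success rule is an inference, but the article states no other rule, and an undefined rule is itself the problem. The exploratory label does not cure it: section 2.6.1 uses that label to separate clinical outcomes from the imaging primary, section 2.3 claims adequate power for the imaging endpoints, and the Discussion looks forward to strong mechanistic evidence.

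Secondly, sections 2.6.2 and 2.9.2 place thresholds and further analysis detail in Supplementary material 3, which is not shown. This stands as a limit: one can say that the article states no rule across modalities, not that none exists. A supplement would still have to narrow an endpoint that the article defines as the whole set.

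Thirdly, the count of nine treats the four DTI metrics as separate families. The ROI family is undefined and may cover them all, and MD is a fixed function of AD and RD, so they cannot be independent. This stands too, and 37% is therefore the high end of the range.

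A reader might also infer two stronger points that the text does not support:

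- Multiplying nine measures by three contrasts gives 1 − 0.95^27 = 75%. This is not an upper bound, and it treats contrasts as independent although any two determine the third. It also presumes uncorrected imaging contrasts, which the article does not specify.
- The two FDR sentences might be read as contradictory. Both can be followed at once; what is unclear is only whether the putamen must also survive the FDR step.

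**Conclusion.** The point holds. The primary endpoint is an unranked set over five modalities, the stated error control stays within each, and no between-arm contrast is named for the primary claim. If any one modality can carry the claim at 0.05, the family-wise error is about 23% for five independent modalities. It is roughly 15% to 37% for correlations from 0 to 0.7 and for five to nine families. A reader might take 23% as a floor, but it is not one, because positive correlation lowers it. Even 15% is three times the nominal level. The figures assume one contrast per family and no further rule in Supplementary material 3. The defect in the endpoint definition does not depend on the exact percentage. The seed rule is ambiguous and needs one clarifying sentence.

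**What to change.** Amend sections 2.6 and 2.9.2, dated before the allocation code is broken:

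1. Name verum minus sham in baseline-to-week-4 change as the primary contrast.
2. Name one summary test per modality. For resting-state fMRI this can be bilateral putamen connectivity, stated to lie outside the seed-level FDR family.
3. Either apply Holm or Bonferroni across the five tests, or name one of them as the single primary test.
4. Make the other seeds, other metrics and all wait-list contrasts secondary, and define the ROI families.

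Which option to take is the investigators' choice. Putamen connectivity is not the automatic sole primary: the article ranks it only among seeds, and the Discussion also hypothesises an effect on nigral iron.

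Cost: no extra scans or patients. Under the split, each modality faces a stricter threshold. At the 90% power that the article uses for UPDRS-III, the smallest detectable difference at 0.01 instead of 0.05 grows by (2.576 + 1.282) / (1.960 + 1.282) = 1.19, about 19% (normal approximation, before any gain from Holm). With a single primary test, the other modalities can no longer carry the primary claim. Either way this changes the primary outcome of a registered trial and must be documented as such.

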##### Unified Parkinson's Disease Rating Scale part III (UPDRS-III)

2.6.1.1

Although all clinical analyses are exploratory, the change in UPDRS-III total score from baseline to week 4 is designated as the primary clinical outcome measure to maintain temporal alignment with the primary neuroimaging assessments. The UPDRS, revised by the Movement Disorder Society (MDS) in 2008 (20), is the gold standard for comprehensive PD symptom assessment (21). The Chinese version of the PD scale has excellent reliability and validity in Chinese PD patients (22). The UPDRS-III evaluates motor function via 18 items scored from 0–4 (higher scores indicate greater impairment). Assessments will occur at baseline, week 4 (post-treatment), and week 8 (end of follow-up; Table 1).

##### Parkinson's disease non-motor symptom scale (NMSS)

2.6.1.2

Non-motor symptoms (NMS) often precede motor manifestations in PD patients and significantly impact disease progression and quality of life (23). The NMSS, developed and validated by the MDS in 2015, is a multidimensional tool that assesses NMS severity and frequency across 52 items within 13 domains (e.g., sleep, mood, gastrointestinal function) on a 0–4 scale. Higher total scores indicate greater non-motor symptom burden (24). NMSS assessments will be conducted at baseline, post-treatment (week 4), and at the end of follow-up (week 8).

##### 39-item Parkinson's disease questionnaire (PDQ-39)

2.6.1.3

The quality of life of PD patients is generally poorer than that of healthy individuals, particularly in terms of physical functioning and mental health (25). The PDQ-39 is a validated patient-reported outcome measure evaluating quality of life in PD across eight domains: mobility, activities of daily living, emotional well-being, stigma, social support, cognition, communication, and bodily discomfort (26). Each of the 39 items is scored 0–4 (higher scores = greater impairment), with total scores transformed to a 0–100 scale for interpretation. PDQ-39 assessments will be performed at baseline, week 4, and week 8.

##### Biomechanical Index

2.6.1.4

Early-stage PD is characterized by reduced arm swing and shortened stride length (27), whereas advanced-stage PD is characterized by impaired balance, postural instability, muscle rigidity, and increased fall risk (28). Pathophysiological overlaps between PD and dystonia further underscore the relevance of biomechanical assessments (29). The FootScan system can be used to quantify gait parameters (step symmetry, center-of-pressure trajectory, temporal/spatial metrics), whereas shear wave elastography (SWE) can be used to evaluate muscle tone improvements. Biomechanical data will be collected at baseline and week 4.

#### Multimodal MRI data

2.6.2

Multimodal MRI data will be acquired at baseline and post-treatment (week 4) via a Siemens Prisma 3.0T scanner (64-channel head coil). All scans will be performed between 4:00–6:00 p.m. Participants will be scanned in the practical “ON” medication state, approximately 1 h after their regular afternoon dopaminergic medication to maintain a uniform medication condition and minimize motion artifacts caused by motor symptoms. No specific dietary restrictions are required before scanning. The post-treatment scan will be scheduled within 24 h after the final acupuncture session. Structural and functional imaging protocols include the following structural markers: T1-weighted imaging (T1WI), T2-weighted imaging (T2WI), T2-Flair imaging, diffusion tensor imaging (DTI), neuromelanin-sensitive MRI (NM-MRI), and susceptibility-weighted imaging (SWI). Functional markers: blood oxygen level-dependent functional MRI (BOLD-fMRI). Detailed acquisition parameters, quality control procedures, preprocessing, and statistical thresholds are provided in Supplementary material 3.

